**Secondary outcomes**					
GSES	x		x	x	
WHOQOL	x		x	x	
FFA	x		x	x	
EDI-2	x		x	x	
EDE-Q8	x		x	x	
CSQ-I			x		x
SUS			x		x
Usage behavior		x			
UTAUT	x				
PHQ-4	x	x	x	x	x
DT	x	x	x	x	x
BMI	x		x	x	
Sociodemographics, medical characteristics	x				

*CESD-R* Center of Epidemiologic Studies Depression Scale-Revised, *GSES* General Self-Efficacy Scale, *WHOQOL* World Health Organization Quality of Life, *FFA* Freiburger Fragebogen zur Achtsamkeit,*EDI-2* Eating Disorder Inventory Bulimia subscales, *EDE-Q8* Eating Disorder Examination Questionnaire, measuring Eating Disorder specific Symptoms, *CSQ-I* Client Satisfaction Questionnaire Internet-based, *SUS* System Usability Scale, *UTAUT* Unified Theory of Acceptance and Use of Technology questionnaire, *PHQ-4* Patient Health Questionnaire-4, *DT* distress thermometer, *BMI* body mass index

A participant who has decided to quit during the intervention counts as a dropout (no login for 6 weeks is considered as a dropout). Patient who drop out of the study will be asked to complete a dropout assessment. The participant who decides to drop out will be contacted (if written permission was given) by study personnel so that the drop-out assessment can be sent to the participant.

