#### Control intervention

In the proposed RCT, the intervention group will be compared with a control group. The intervention will be compared to the usual care the participants receive in conventional healthcare in Germany. Hence, there is no restriction regarding access to therapeutic and/or medical services during the trial. Besides that, the participants in the control condition do not receive any additional treatment. The control group participants will not have access to any content of the LightMood intervention. Instead, they will receive every week notifications via mail for the in-treatment assessment, which will be conducted online by the participants.

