*Eating disorder symptoms:* The Bulimia Subscale of the Eating Disorder Inventory-2 [30] and the Eight-Item Short Version of the Eating Disorder Examination Questionnaire [31] are used to record eating disorder-specific symptoms. The EDI-2 bulimia subscale consists of 7 items measuring symptoms of bulimia, with a focus on binge eating [30]. Items are measured on a 6-point Likert scale ranging from 0 (never) to 6 (always). The total score ranges from 0 to 42. The EDE-Q8 is also used to assess the psychopathology of eating disorders. The EDE-Q8 contains two items each on the subscales restraint, concern about eating, concern about weight, and concern about body shape. The EDE-Q8 consists of 5 items measuring the psychopathology of the eating disorder over the past 28 days on a 7-point Likert scale from 0 (no day) to 6 (every day), and 3 items measuring occurrence and assess the frequency of core eating disorder behaviors on a scale from 0 (never) to 6 (every time) [31].
*BMI*: Body mass index is a measure of an individual’s body weight in relation to their height. Height and weight are recorded via self-reports [32].
*Treatment satisfaction:* The Client Satisfaction Questionnaire [33], adapted to Internet-based interventions, is used to record treatment satisfaction. The CSQ-I consists of 8 items, which are answered with a 4-point Likert scale. The CSQ-I is a measure for considering user satisfaction in the overall evaluation of eHealth interventions.
*Usability:* The System Usability Scale [34] is used to measure usability. The SUS consists of 10 items, which are answered with a 5-point Likert scale. The SUS is a measure for evaluating the usability of a system.
*Usage behavior:* The time to dropout and the usage behavior are calculated based on the number and type of modules completed, the time per day, the type and number of modules started, the time since the last login, the frequency of login, the frequency of each module, the time spent on each module, the percentage of each module completed, the type and number of videos and audios started, and the type and number of videos and audios finished. The data is assessed via the backend of the intervention.
*Predictors of usage behavior:* To measure predictors of usage behavior, the validated Unified Theory of Acceptance and Use of Technology questionnaire [35] is used. The UTAUT evaluates health-related Internet use, the acceptance of eHealth measures, and the barriers and resources of eHealth use.

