^2^ tests (or Fisher’s exact tests for variables with small cell sizes) will be utilized. Further mixed ANOVAs will be used to assess the impact of the intervention on the secondary outcome measures, such as eating behaviors (see Table 1). Also here, we will resort to more robust models in case of a violation of assumptions. Also, in case of a significant effect of our intervention on the primary outcome, we will assess whether this result is mediated by increases or decreases in scores concerning eating behavior. Here, we will use mediation analyses on mixed linear models or robust alternatives (such as mixed linear models with bootstrapping). We will not perform subgroup analyses. Additionally, analyses of variance and *χ*
^2^ tests will be employed to examine potential differences in sociodemographic and clinical data among various subgroups, such as dropouts, participants who completed the intervention, and those who benefitted from the intervention.

Exploratory analyses, including regression analyses, will be conducted to investigate the relationship between usage behavior and clinical outcomes, considering all assessments including in-treatment assessments. Secondary endpoints will include the examination of time to dropout using the Kaplan-Meier estimate and Cox proportional hazards regression. Here, a standard proportional hazards model—using the *coxph* function from the *survival* package in R—will be applied. Differences in time to dropout between the treatment and the control group will be assessed. Also, the baseline values of the relevant psychometric measures of depression and mental distress (CESD-R, PHQ-4, DT), self-efficacy (GSES), quality of life (WHOQOL), and eating behavior (EDI-2, EDE-Q8), as well as sociodemographic and medical characteristics (gender, SES, BMI), will be entered into the regression model to explore potential determinants of dropout. In case of large deviations from constant hazards (which will be tested using the *cox.zph* function from the abovementioned package), we will explore underlying reasons and might, for instance, further assess non-linear effects or models with stratification according to certain covariates.

To ensure safety assessment, separate tabulations and line listings of adverse events and severe adverse events will be generated for comprehensive analysis.

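### Time to dropout is compared between arms, but its login and module component cannot be applied to controls in the same way

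*Protocol article*

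**What the plan says.** Four statements in the Protocol article bear on this.

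- **Comparison (Statistical methods).** "Secondary endpoints will include the examination of time to dropout using the Kaplan-Meier estimate and Cox proportional hazards regression", followed by "Differences in time to dropout between the treatment and the control group will be assessed".
- **Event (Study design, text below Table 1).** "A participant who has decided to quit during the intervention counts as a dropout", with the addition that "no login for 6 weeks is considered as a dropout". This is the only dropout rule given, and it has no variant for the control arm.
- **Derivation and data source (Outcomes, usage behavior).** "The time to dropout and the usage behavior are calculated based on the number and type of modules completed", together with login frequency, time since last login, time per module, and video and audio use. On the source: "The data is assessed via the backend of the intervention".
- **What controls receive (Control intervention).** "The control group participants will not have access to any content of the LightMood intervention". They get a weekly notification to complete an online in-treatment assessment. Trial procedure and timeline likewise gives LightMood access to the intervention group only. Whether the control assessment needs a login is not stated.

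**The concern.** A time-to-event comparison between randomized arms needs one event, ascertained by the same rule in each arm. Here part of the event is inactivity in an application that only one arm can use. In the LightMood arm, dropout can mean that someone stopped opening the app while still willing to answer questionnaires. In the TAU arm there is no app to stop using, so dropout has to mean something else: a declared decision to leave or, at best, no longer answering the weekly assessment.

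At stake is a between-arm retention result that readers would take as evidence on whether LightMood keeps people in the study or drives them out. If ascertainment differs by arm, curves can separate without any difference in retention, or a real difference can be hidden. This is a conflict between rules the article states, and not a detail merely left to an analysis plan.

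**Working it through.** The article gives no hazard ratio, event count or power for time to dropout, so there is no figure to reproduce. The check sets the stated rules side by side and then illustrates the mechanism.

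**Step 1: each component of the event, by arm**

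| Component | LightMood | TAU |
|---|---|---|
| Active decision to quit | Can occur | Can occur; the article treats TAU as a condition that also lasts 4 months |
| 6 weeks without login | Recorded in the backend | No LightMood content to log in to; a login for the weekly assessment is possible but not stated |
| Modules, time per module, video and audio use | Recorded in the backend | Do not exist |

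**Step 2: the possible readings for controls**

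- *No control logins are recorded.* The login rule either flags every control at week 6 or cannot be applied. In the second case controls can drop out only by declaring it, while LightMood participants can drop out by declaring it or by inactivity.
- *Questionnaire logins are counted.* The event becomes stopping app use in one arm and stopping questionnaires in the other.

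Neither reading gives the same event in both arms.

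**Step 3: can login habits alone produce an arm difference?**

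Assumptions, none of which the article gives for this endpoint:

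- 17 weeks, to represent 4 months.
- The same true quitting in both arms, 30% by week 17, at a constant weekly hazard h = 1 − 0.7^(1/17) = 0.0208.
- The event is six consecutive weeks without login.
- p is the weekly probability of logging in among those who have not quit.

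Arithmetic check: if everyone who has not quit logs in every week (p = 1), only those who quit by week 12 can complete six silent weeks by week 17. That gives 1 − 0.7^(12/17) = 0.223, and the simulation gave 0.223.

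Simulated results, with rates as events per person-week:

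| p | Flagged by week 17 | Event-rate ratio against p = 0.9 |
|---|---|---|
| 0.9 | 22.4% | 1.00 |
| 0.7 | 23.3% | 1.05 |
| 0.5 | 31.2% | 1.46 |
| 0.4 | 42.4% | 2.09 |
| 0.3 | 59.9% | 3.29 |

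True quitting is identical in every row. When login habits are similar and frequent the artefact is negligible; when they differ widely it is large. The article gives no information on which row applies to which arm.

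**The case against.** The strongest defence has four parts.

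1. **Active quitting applies to both arms.** The rule speaks of quitting during the intervention period, the next sentence refers to leaving the study, and both conditions last 4 months. This stands: part of the event is common to both arms. It does not remove the inactivity rule or the backend derivation.
2. **Controls may have a login.** They are withheld LightMood content, not necessarily an account, and they complete weekly assessments online. This also stands as a possibility. A reader might infer that dropout cannot be observed in controls at all, but the article does not establish that.
3. **The illustration depends on chosen login probabilities.** Controls are prompted weekly, LightMood trainings are paced weekly with notifications, and at 0.7 against 0.9 the ratio is only 1.05. This is correct. The table shows a mechanism and does not estimate the bias in this trial.
4. **A condensed article may leave event dating and censoring to the analysis plan.** That is fair for detail. Here, however, the article itself fixes the rule, the data source and the between-arm comparison, and these do not fit together.

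Two further criticisms may tempt a reader. One is that the Cox model is overloaded: 128 × 0.30 = 38.4 events over at least 11 terms (arm plus ten listed covariates) is 38.4 / 11 = 3.5 per term. But the 30% is the sample-size rate from T0 to T3, which includes loss to follow-up and so counts a different event. The covariates also serve a stated exploratory aim, so a shorter list would be a modelling preference. The other is the phrase "In case of large deviations from constant hazards". It is a wording slip without consequence, because the section names the proportional hazards model and the functions that fit and check it.

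**Conclusion.** The point holds as a mismatch between the event definition and the between-arm comparison. As written, the login and module part of dropout cannot be applied alike to LightMood and TAU participants, so an observed arm difference may reflect the measurement rule and not retention.

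The size cannot be derived from the document. Ratios of 1.05 to 3.29 with no difference in quitting are illustrative and rest on the assumed login probabilities, the 17-week window and the 30% quitting rate. A reader might go further and call the bias unbounded, or the hazard ratio meaningless. The documents do not support either: the active-quitting component is shared, and controls may have recorded logins.

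The consequence is confined to one secondary endpoint on retention. The primary ANCOVA of CESD-R at T1 is not directly affected. The change should be made before analysis, but it does not threaten the trial's main conclusion.

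**What to change.** For the between-arm Kaplan-Meier and Cox analyses, define one study-attrition event that can be observed identically in both arms: withdrawal from the study, or the first scheduled assessment missed with none completed afterwards, dated by that assessment. Use only assessments on the same schedule in both arms. T1, T2 and T3 qualify. The in-treatment assessments also qualify if their frequency is the same; the article states weekly notifications for controls but does not state the frequency in the LightMood arm.

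Report login- and module-based disengagement, including the 6-week rule, separately as adherence in the LightMood arm only, and give the two events different names.

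The cost is analysis wording only, because these assessments are already planned online in both arms. The downside is that the between-arm result no longer describes app disengagement. If only T1 to T3 can be used, event times also become coarse (months 4, 5 and 7).

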#### Patient and public involvement

Patient engagement was a key aspect in the development of the intervention and the planning of the proposed trial. The intervention itself was designed using a user-centered design approach [22]. Additionally, we have conducted assessments to evaluate the acceptance of such an e-mental health intervention and identify potential drivers and barriers to its usage [17].

Patient representatives actively participated in creating patient-friendly summaries and consent forms. Furthermore, we will maintain close collaboration with patient representatives and self-help organizations to ensure effective dissemination of the trial results within the target group. To enhance accessibility, the comprehensibility, illustration, and processing duration of the final case report forms were tested.

To keep the public informed, the trial results will be published in scientific journals and presented at professional congresses. Moreover, the findings will be shared in easy-to-understand language on social media channels and the study website. This approach aims to make the results accessible and understandable to a wider audience.

## Discussion

In our prospective, randomized controlled LightMood trial with two parallel arms, we aim to assess the efficacy of a manualized, user-centered, e-mental health intervention for participants with obesity to reduce depression symptoms. The aim is to offer an evidence-based, efficient, low-threshold online intervention.

The provision of care via digital approaches aims to keep costs low for treating staff and premises, to offer support to many people at the same time, to promote continuity of care by being independent of time and place, and to overcome the insufficient availability of specialized treatments by improving outreach. Thus, the intervention has socioeconomic and health-economic benefits. By evaluating the efficacy of the LightMood intervention, relevant findings for e-mental health interventions in general and in the context of obesity and mental health burden could be derived. Accordingly, other patient groups could benefit from similar e-mental health approaches as well. Exploring relations between actual usage behavior and mental health outcomes could be of particular interest to eHealth research in general.

Several guidelines emphasized the importance of dealing with the psychological aspect of obesity, such as improving self-esteem, body image, quality of life, and the treatment of depression [9]. The initial results of e-mental health interventions have been promising for people with obesity [19–21]. Accordingly, RCTs are needed to evaluate e-mental health interventions in obese. Given the increasing impact of digital technologies in daily life, the online LightMood intervention has the potential to reach a high number of people with obesity and to overcome barriers that patients face in analog fact-to-face care (e.g., long waiting times for psychotherapy).

Due to its accessibility everywhere at any time, the LightMood intervention enables people with obesity and mental health burden to participate in an online intervention regardless of barriers in the current healthcare system.

However, the trial has some limitations. The study only includes participants with access to the Internet, as access is required in the intervention. Furthermore, blinding to group allocation of the patients is not possible due to the nature of the present trial. However, this is a common issue in digital health trials. Assessors and statisticians will be blinded.

In conclusion, this intervention is addressing a large treatment and research gap, based on the fact that there are very few digital interventions targeting this population. On top of that, this intervention has the strengths of their user-centered approach and combined treatment of depression and obesity.

## Trial status

The LightMood trial is not yet recruiting as of the date of the publication. The planned date of recruiting is the first of August 2023. Recruitment is expected to be completed in May 2024. This trial has been approved by The Ethics Committee of the Medical Faculty of the University Duisburg-Essen (protocol version #1, dated July 2023, drks.de #22-10882-BO).

## Data Availability

In accordance to the Good Clinical Practice guidelines, important trial data will be archived for 10 years after the trial’s completion or termination. Patient documents will be stored in compliance with hospital regulations, and access to stored data during and after the trial will be restricted to authorized staff only. Once the major results of the trial are published, the collected data will be made available in an anonymous format upon reasonable request. Additionally, we will store and provide access to the statistical analysis plan and other relevant documents upon request. Access to the data storage will be limited to authorized personnel exclusively.

## Abbreviations

CBT: Cognitive behavioral therapy
TAU: Treatment as usual
MBSR: Mindfulness-based stress reduction
ACT: Acceptance and commitment therapy
CESD-R: Center of epidemiologic studies depression scale-revised
GSES: General self-efficacy scale
WHOQOL: World Health Organization quality of life
FFA: Freiburger Fragebogen zur Achtsamkeit
EDI-2: Eating Disorder Inventory Bulimia subscales
EDE-Q8: Eating disorder examination questionnaire, measuring eating disorder specific symptoms
CSQ-I: Client satisfaction questionnaire internet-based
SUS: System usability scale
UTAUT: Unified theory of acceptance and use of technology questionnaire
PHQ-4: Patient health questionnaire-4
DT: Distress thermometer
BMI: Body mass index
